### Serious adverse events

Like other physical activities, Yoga is known to be safe.^10^ Information will be collected on serious adverse events (including death) occurring in participants that may be attributed to the interventions. Based on medical and scientific judgement, an independent clinician will determine the relationship of any event to the interventions.

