### Interventions

#### Intervention (YOGA-DP)

YOGA-DP is a structured lifestyle education and exercise programme, provided over a period of 24 weeks (see table 2). The exercise part is based on Yoga and includes Shithilikarana Vyayama (loosening exercises), Surya Namaskar (sun salutation exercises), Asana (Yogic poses), Pranayama (breathing practices) and Dhyana (meditation) and relaxation practices. Online supplementary table S1 shows the structure and content of the Yoga sessions. The programme is delivered by YOGA-DP instructors—qualified and experienced Yoga teachers with formal training provided on the intervention. Female instructors are available for female participants. Group Yoga sessions are run locally (such as at these Yoga centres and community centres) at different time points of the day (with evening and weekend sessions), and participants can join as per their convenience. We are reimbursing some of their local travel costs for attending the sessions. A family member or someone close to the participant is invited to join them in the sessions. Once participants complete the programme, they are strongly encouraged to maintain a healthy lifestyle in the long-term, using the intervention booklet and a video.

10.1136/bmjopen-2019-036277.supp1Supplementary data

**Table 2 T2:** Structure of YOGA-DP

Week	Group Yoga sessions delivered by YOGA-DP instructors	Self-practice of Yoga at home using YOGA-DP booklet and a video	Extra features
1–4 (month 1)	At least two sessions of 45 min per week. An attendance register is kept.	–	At the first session, the instructor is giving participants part one of our programme booklet. This gives them information about being at high risk of T2DM and how to prevent T2DM (ie, by being more physically active, keeping a healthy weight, eating less fat (especially saturated fat) and eating more fibre).
5–12 (month 2–3)	At least two sessions of 75 min per week. An attendance register is kept.	–	At the last session, the instructor is giving participants part two of our programme booklet and a video. These give them information on Yoga practice to prevent T2DM. Also, a Yoga diary and non-slippery Yoga mat are provided for self-practice of Yoga at home.

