13–24 (month 4–6)	At least one session of 75 min every 4 weeks. An attendance register is kept.	At least two sessions of 75 min per week. Participants are given the Yoga diary to record their Yoga practice (types and minutes).	The instructor is phoning participants every week to offer support and help and to troubleshoot any problems.
25+ (month 7+)	–	At least two sessions of 75 min per week. Participants are given the Yoga diary to record their Yoga practice (types and minutes).	–

T2DM, type-2 diabetes; YOGA-DP, Yoga programme for T2DM prevention.

Intervention fidelity will be ensured through regular training of YOGA-DP instructors, based on the manual developed for them. Also, sessions will be regularly observed and assessed with a checklist to ensure that they are being delivered as per the manual. To improve performance, structured and instructive feedback will be provided.

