### Study parameters and data collection

#### Randomised controlled trial

SD of the outcome measure (mentioned before), which will be used to calculate the main RCT sample size.Recruitment—number of people approached to participate, written informed consent given, screened for eligibility, found eligible and randomised.Intervention adherence—number of sessions attended out of the 27 sessions, number who self-practice at home and frequency and duration of self-practice at home.Follow-up—number of randomised participants followed-up at 6 months.Potential contamination—number of control group participants participating in any Yoga class during 6-month follow-up (self-reported).Time needed to conduct the study (eg, to recruit participants).See table 1.

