### Participant withdrawal

Participants will be withdrawn from the study either at their request or at the discretion of the site investigator for example, if diagnosed with diabetes (will receive the standard treatment) or if no longer safe to participate in physical activities (determined by PAR-Q/clinician).^29^ They will be made aware that this will not affect their future care. Also, they will be made aware (via the participant information sheet and consent form) that should they withdraw, the data collected to date will not be erased and may still be used in the final analyses.

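### Stated harms collection covers only serious events already thought attributable, so the trial could not describe the programme's tolerability by arm

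*Protocol article*

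**What the plan says.** The section on serious adverse events in the protocol article sets the rule: "Information will be collected on serious adverse events (including death) occurring in participants that may be attributed to the interventions". It opens from the premise "Like other physical activities, Yoga is known to be safe" and ends by saying that "an independent clinician will determine the relationship of any event to the interventions".

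The programme itself is described thus: "YOGA-DP is a structured lifestyle education and exercise programme, provided over a period of 24 weeks". Table 2 moves most practice to the home from week 13. There, "Participants are given the Yoga diary to record their Yoga practice (types and minutes") and, in weeks 13–24, "The instructor is phoning participants every week to offer support and help and to troubleshoot any problems". The control arm receives a leaflet.

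The section on participant withdrawal foresees removal from the study, among other grounds, "if no longer safe to participate in physical activities (determined by PAR-Q/clinician"). Among the feasibility parameters, follow-up is defined as "number of randomised participants followed-up at 6 months", and adherence as sessions attended plus the amount of home practice. Under Randomisation, participants and providers know the allocation and the outcome assessors do not.

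**The concern.** The collection rule applies two filters: the event must be serious, and someone must already think that an intervention may have caused it.

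The first filter leaves out strains, minor falls and joint pain. For poses and sun salutations in people aged 18 to 74, partly practised at home, these are the harms one would most want described. The introduction faults earlier Yoga studies because it is hard to tell how carefully safety and acceptability were considered, so tolerability of this newly developed programme is a natural product of a feasibility trial.

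The second filter puts a causality judgement at the point of collection, ahead of the clinician appointed to make it. The article does not say who applies it. If unblinded staff do, selection could differ by arm.

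The Discussion makes adherence and follow-up part of the decision on the main trial. If some people stop because they were hurt, the investigators would want to know that when deciding whether to change the programme.

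**Working it through.** **Step 1: does any other section widen the rule?** No figure in the plan is in dispute, so the main check is a reading of every place where data are collected.

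| Place in the protocol article | What it provides on harms |
|---|---|
| Serious adverse events | Serious and possibly attributable events; covers both interventions, so both arms |
| Table 1 (baseline and 6 months) | No adverse-event or injury item; the quality-of-life item refers only to the moment of completion |
| Table 2, Yoga diary | Types and minutes of practice only |
| Table 2, weekly calls | Support and problem-solving; no event recording stated; Yoga arm only |
| Study parameters | Counts for recruitment, adherence, follow-up and contamination; no harms item |
| Participant withdrawal | Foresees safety withdrawals; links no event record or coded reason to them |
| Qualitative evaluation | Interviews with up to 20–30 purposively sampled participants, non-completers included; not systematic |

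Nothing widens it.

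**Step 2: the order of the causality judgement.** Collection is limited to events that may be attributable, and the independent clinician then judges relationship. An event that nobody at the site suspects never reaches the clinician. The clinician can remove a suspected link but cannot add a missed one.

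**Step 3: illustration of size.** Inputs from the document: 32 per group and 20% expected loss at 6 months (Sample size estimation). The per-person 6-month risks are assumptions, because the document gives none. The chance of at least one event among n people at risk p is 1 − (1 − p)^n.

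- Serious attributable event, n = 32: p = 0.5% gives 1 − 0.995^32 = 15%. The range 0.2% to 1% gives 6% to 28%. Expected count at 0.5%: 32 × 0.005 = 0.16.
- Non-serious injury, n = 32: p = 5% gives 1 − 0.95^32 = 81%. The range 3% to 10% gives 62% to 97%. Expected count at 5%: 32 × 0.05 = 1.6.
- A question asked at 6 months reaches fewer people: 32 × (1 − 0.20) = 25.6, about 26. At 5% this gives 1 − 0.95^26 = 74%. The range 3% to 10% gives 55% to 94%.
- Zero events in 32: the exact one-sided 95% upper limit is 1 − 0.05^(1/32) = 8.9%.

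If serious attributable events are as rare as assumed, the chance that the Yoga arm records none is 100% − 15% = 85% (72% to 94%). The 8.9% limit depends on the size of the arm, not on the collection rule. It shows only how little an observed zero would exclude.

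**The case against.** The strongest reply is that this is a condensed article and that the sentence stands under a heading about serious events. A statement of what is collected under that heading does not say that nothing else is collected, and case-report-form detail belongs to the full protocol. This stands in part. That harms collection stops there is inferred from the absence of any other provision. But the sentence does state which events count, and it is the only statement of harms scope in the article.

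A reader might go further and infer that injuries go unrecorded even when they end participation, or that drop-out from injury could not be told apart from loss of interest. The article does not support either. A withdrawal for being unsafe to exercise rests on a PAR-Q or clinician determination, so the site would know the reason, and interviews include non-completers. These sources are partial, but they exist, and the full protocol may record reasons.

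A reader might also infer that the weekly calls would bias harm counts between arms. The article states no event recording on those calls, so this becomes an issue only if events heard there are later counted.

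Nor do the documents show that the programme is likely to injure people. They describe a gentle approach, cite a review with no major safety issues, and screen for readiness to exercise. The expectation that non-serious injuries are the main foreseeable harm is a judgement made here, and the 15% and 81% follow from the risks chosen.

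Finally, safety is not a listed feasibility parameter and the trial is not powered for it. That is true, but the proposal is description, not a test.

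**Conclusion.** The point holds as a limitation of the stated design. The rule covers only serious, possibly attributable events in either arm; no other section provides for systematic recording of non-serious injuries; and the attribution filter comes before the independent judgement. Followed as written, the plan would probably yield few or no harms and no account of tolerability by arm. No stated procedure captures withdrawal or non-adherence due to injury, beyond what clinician or PAR-Q determinations and sampled interviews happen to reveal.

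The conclusion that few or no harms would be reported assumes that serious attributable events are rare (0.5%; range 0.2% to 1%). How much is lost depends on the true rate of non-serious injury, which the documents do not give. This should be corrected, but it does not undermine the main purpose of the trial, which is to estimate the SD and the other feasibility parameters.

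**What to change.** 1. Record all serious adverse events in both arms regardless of suspected attribution, and leave relationship to the independent clinician.
2. At the 6-month assessment, ask both arms one identically worded question: any injury, fall or new pain since randomisation that needed care or stopped activity for a day or more.
3. Record injury as a coded reason for withdrawal. This is needed because people who withdraw may never complete the 6-month form.
4. Report counts by arm descriptively, without a test. List any events heard on the weekly calls separately as Yoga-arm information, since controls have no calls.

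If the full protocol already does this, it is enough to say so and to correct the scope sentence.

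The cost is one question on an existing form, one withdrawal code and one descriptive table. The downsides are slight extra form time and recall error over 6 months. An answer could also reveal allocation, so the question is best asked after the blinded measurements. No eligibility, withdrawal or treatment rule changes.

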### Participant withdrawal

Participants will be withdrawn from the study either at their request or at the discretion of the site investigator for example, if diagnosed with diabetes (will receive the standard treatment) or if no longer safe to participate in physical activities (determined by PAR-Q/clinician).^29^ They will be made aware that this will not affect their future care. Also, they will be made aware (via the participant information sheet and consent form) that should they withdraw, the data collected to date will not be erased and may still be used in the final analyses.

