Health interventions should be informed by and compatible with the sociocultural expectations of people and their health beliefs.^21^ Yoga is such an intervention in India. The Indian government is committed to and has prioritised the prevention and management of chronic diseases like T2DM through traditional Indian therapies like Yoga. The Ministry of AYUSH is dedicated exclusively towards traditional Indian therapies.^22^ There is, therefore, a need for a definitive, robustly designed study to assess the utility of Yoga in T2DM prevention among high risk people in India. The principal research question to be addressed by the main RCT is whether YOGA-DP is effective in preventing T2DM among high risk people in India as compared with enhanced standard care. The primary outcome of the main RCT will be the difference in mean fasting plasma glucose level between the two treatment arms. We intend to do long-term (≥1 year) follow-ups in the main RCT. The chances of successful completion of a costly T2DM prevention RCT will improve if the feasibility of its key elements is checked before it starts.^23 24^ Important parameters, needed to design the main RCT, will be estimated.^23^ Thus, in this current study, we are determining the feasibility of undertaking the main RCT.

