### Sample size estimation

#### Randomised controlled trial

At least 64 participants (32/group) will be adequate to precisely estimate the SD of the outcome measure (fasting plasma glucose level at 6-month follow-up). This is calculated in relation to the desired level of confidence (95%) for the SD, the chosen power (80%) and significance level (5%, two-tailed) of the analysis in the main RCT and the expected loss to follow-up (20% at 6 months) in the current study.^25 26^

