### Data analyses

#### Randomised controlled trial

Baseline characteristics and important parameters such as follow-up will be summarised and compared between the two study arms using numbers and percentages for categorical data and summary measures of mean or median and spread for continuous data. Being a feasibility RCT, it is not adequately powered to detect a difference in outcomes between the two study arms. However, appropriate regression methods will be used to get initial estimates of effects with CIs to guide the design of the main RCT. All primary analyses will be based on the intention-to-treat principle and will be unadjusted. Subsequently, the adjustment will be done for the baseline data and site. No interim analysis is planned.

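### Withdrawal from the study on a diabetes diagnosis, with no later outcome collection described, can leave 6-month glucose missing for a reason tied to the outcome

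*Protocol article*

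**What the plan says.** Under Participant withdrawal, the protocol article allows a participant to be "withdrawn from the study either at their request or at the discretion of the site investigator for example, if diagnosed with diabetes". A second example is a participant who is no longer safe for physical activity. A participant diagnosed with diabetes receives the standard treatment. On data, the section says only that "should they withdraw, the data collected to date will not be erased and may still be used in the final analyses". It describes no outcome collection after withdrawal.

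Four other places bear on this:

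- **Sample size estimation:** the trial is sized to "precisely estimate the SD of the outcome measure (fasting plasma glucose level at 6-month follow-up".
- **Study parameters and data collection:** that SD is a listed parameter, "which will be used to calculate the main RCT sample size". The number of randomised participants followed up at 6 months is another.
- **Introduction:** "The primary outcome of the main RCT will be the difference in mean fasting plasma glucose level between the two treatment arms".
- **Data analyses:** "All primary analyses will be based on the intention-to-treat principle and will be unadjusted".

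Table 1 schedules FPG and glycated haemoglobin at baseline and at the final 6-month visit, with none in between.

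**The concern.** Diabetes is recognised by high glucose or high glycated haemoglobin, so this withdrawal reason is close to being a value of the outcome itself. Participants enter with FPG of 5.6 to 6.9 mmol/L, next to the diabetic range, and the programme exists to stop them crossing it. If those who cross leave the study before the 6-month sample, the missing values tend to be the high ones.

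Three quantities are exposed:

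- **The SD.** Losing high values narrows the observed distribution, and a main trial sized on too small an SD is too small.
- **The effect estimate.** It moves towards zero or away from it, depending on which arm loses the values.
- **The follow-up count.** People who could have attended are counted with those who were truly lost.

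Removing randomised participants because of an event after randomisation also runs against an intention-to-treat analysis. The physical-activity example has the same gap: it may bear on taking part in Yoga, but it gives no reason to forgo a blood test, least of all in a control arm that receives a leaflet.

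**Working it through.** **1. The plan's own figure.** The required precision for the SD is not stated, so 64 cannot be fully re-derived. The allowance for 20% loss is consistent: 25 / 0.8 = 31.25, rounded up to 32 per group; 51 / 0.8 = 63.75, rounded up to 64. Expected evaluable number: 64 × 0.8 = 51.2. With 50 degrees of freedom, the chi-square 95% confidence interval for the SD runs from 0.84 to 1.24 times the estimate.

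**2. Who can lose the outcome.** Table 1 has no glucose or glycated haemoglobin test between baseline and 6 months. A diagnosis made from the 6-month sample comes with the value already collected, and the withdrawal section allows its use. The loss is confined to people diagnosed earlier, mainly outside the trial. Their share is unknown, so it is a free parameter *q* below.

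**3. Inputs.**
- From the document: 80% power, 5% two-sided, 1:1 allocation, entry FPG 5.6 to 6.9 mmol/L.
- Assumed: 6-month FPG normal; control mean 6.2; true difference 0.2 or 0.3 (intervention mean 6.0 or 5.9); SD 0.5, 0.7 or 0.9; cut-off *c* = 7.0, just above the stated entry limit. All in mmol/L. The document gives no 6-month mean, SD, effect or diabetes incidence.

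With means of 6.0 to 6.2, these assumptions put 2% to 19% of participants at or above 7.0, about 1 to 10 of 51.

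**4. Formulas.** With a = (c − μ)/σ, p = 1 − Φ(a), R = 1 − qp and h = qφ(a)/R:

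- observed mean = μ − σh
- observed SD / true SD = √(1 − ah − h²)
- pooled ratio r = root mean square of the two arms' ratios
- main-trial size relative to need = r²
- power ≈ Φ(2.80 r − 1.96)

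**5. One case in full: SD 0.7, difference 0.2, half lost (q = 0.5).**
- Control (6.2): a = 1.143, φ = 0.2076, p = 0.1265, R = 0.9367, h = 0.1108. SD ratio = √(1 − 0.1267 − 0.0123) = 0.928. Observed mean = 6.122.
- Intervention (6.0): a = 1.429, φ = 0.1438, p = 0.0766, R = 0.9617, h = 0.0748. SD ratio = 0.942. Observed mean = 5.948.
- Pooled r = 0.935, r² = 0.874, power ≈ Φ(0.66) ≈ 0.745. With whole participants: 169 planned per arm against 193 needed, power 0.747.

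**6. The whole grid, same *q* in both arms.**

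| Share of values ≥ 7.0 lost | Pooled SD / true | Size / needed | Power | Observed / true difference |
|---|---|---|---|---|
| none | 1.00 | 1.00 | 80% | 1.00 |
| a quarter | 0.97–0.98 | 0.93–0.97 | 77–79% | 0.93–0.97 |
| a half | 0.92–0.97 | 0.85–0.93 | 73.5–77.5% | 0.85–0.93 |
| all (upper bound) | 0.79–0.93 | 0.63–0.86 | 61–74% | 0.63–0.86 |

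**7. Direction of the effect bias.** In the case of step 5 the true difference is 0.20. Loss in both arms gives 6.122 − 5.948 ≈ 0.175. Loss in the intervention arm only gives 6.2 − 5.948 = 0.252. Loss in the control arm only gives 6.122 − 6.0 = 0.122. The sign depends on how withdrawals fall between the arms.

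**8. Follow-up count.** Each such withdrawal takes 1/64 = 1.6 percentage points off the follow-up rate. The count is correct under this rule, but it understates what is achievable if the main trial drops the rule.

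**The case against.** The rule is discretionary and diabetes is only an example. Since the trial does no interim glucose testing, most diagnoses it makes itself would come from the 6-month sample, whose value is kept. The trial is expressly not powered for effects, and the sampling interval for the SD (0.84 to 1.24) is wider than the shifts in the partial-loss rows. Participants diagnosed early receive standard treatment, so their later values would not restore the untreated upper tail that the model takes as the truth. Handling of missing values may be set out in an analysis plan that is not shown.

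Much of this stands. A reader might infer that the rule removes the whole upper tail; the document does not support that, and full loss is only a bound. A reader might also infer a bias in favour of Yoga, because intervention participants attend sessions and, in weeks 13 to 24, "The instructor is phoning participants every week to offer support and help". But those contacts are with Yoga instructors, no glucose testing is described in them, and the same rule applied equally in both arms shrinks the difference.

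The objection does not remove the point. The rule is stated, not merely left out of a condensed article: it takes people out of the study and mentions only data already collected. Sampling error is allowed for by the trial's size, whereas this shift goes one way for the SD and can be avoided. An analysis plan cannot recover a value that was never taken, and discretion lets the two sites apply the rule differently.

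**Conclusion.** The point holds in a conditional form. As written, the rule can leave 6-month FPG missing for reasons tied to the outcome in participants diagnosed before the 6-month sample, and it needs reconciling with the intention-to-treat commitment. The SD can be too low, the effect estimate can be off in either direction, and the follow-up count mixes two kinds of loss.

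If a quarter to a half of the values at or above 7.0 mmol/L are lost, the SD falls by roughly 2% to 8%, and a main trial sized on it has about 73% to 79% power instead of 80%. If no one is diagnosed before the sample, there is no bias by this route. These figures rest on the assumed normal distribution, means, SDs and cut-off, and treat untreated FPG as the target. The safety route was not modelled, and nothing in the document links it to high glucose.

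The issue also matters for the main trial if the rule is carried over: the intended follow-up of at least 1 year leaves more time for diagnoses before the final sample.

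**What to change.** Amend the Participant withdrawal section:

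- Separate stopping the intervention from ending outcome collection.
- Invite participants withdrawn by the investigator to the planned 6-month assessment, and analyse them in their randomised arm, unless they withdraw consent.
- Flag FPG values taken after diabetes treatment started, and run a sensitivity analysis on how they are handled.
- Report investigator withdrawals by arm and reason, separately from loss to follow-up.

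Clinical care after a diagnosis or a safety concern is left exactly as it is.

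The cost is a one-paragraph amendment and an already scheduled visit for a few people. The downside is that some values will be under treatment, so they need the flag and the sensitivity analysis and will not fully restore the untreated distribution.
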